## Abstract

**Background:**

The high burden of bereavement in sub-Saharan Africa is largely attributable to HIV, cancer, and other non-communicable diseases. However, interventions to improve grief and bereavement are rare. Given high rates of mortality in the context of weak health systems, community lay members are well placed to provide peer bereavement support. The 9-cell bereavement tool was developed in Zimbabwe to improve community members’ capacity to support the bereaved. This study aims to determine the feasibility of implementing the 9-cell bereavement tool and recruitment to experimental evaluation.

**Methods/design:**

This feasibility cluster randomized trial with embedded qualitative interviews will be conducted in two comparable neighborhoods in Zimbabwe. Community leaders from each neighborhood will identify 25 potential community lay bereavement supporters, each of whom will recruit 2–3 bereaved community members into the trial. The intervention will be randomly allocated to one community, and the second community will form a wait-list control (*n* ≥ 75 in each community cluster). Recruitment is estimated to take place over 3 weeks. Measures at T0 (baseline, i.e., week 0), T1 (midline, i.e., week 14 or 3 months post-baseline) and T2 (endline, i.e., week 27 or 3 months post-midline) will address mental health, social support, and levels of grief per individual. Qualitative data will describe lay supporters’ views of intervention training and delivery, and participants’ experience of bereavement support.

**Discussion:**

This is the first documented trial evaluating a bereavement intervention in sub-Saharan Africa. Recruitment, retention, and measurement data will determine the feasibility of a full trial.

**Trial registration:**

ISRCTN, ISRCTN16484746. Registered 6 February 2018

## Background

Bereavement is the process during which grief is experienced over time [1]. Both grief and bereavement are subjective in their experience and duration. Bereaved individuals who have not been through the process of grief have an increased risk of mortality [2, 3], deterioration of physical health [2], reduced cognitive functioning, increase in mental health challenges, and associated illnesses [4]. These outcomes negatively impact the socio-economic status of individuals while generating high costs in already fragile economies of low-income countries [5, 6]. Bereavement support is therefore an essential and core component of palliative care defined by the WHO [7, 8].

Bereavement is an under-researched field in African countries, despite high mortality rates from communicable diseases such as HIV, tuberculosis, and malaria; and non-communicable diseases such as cancer, heart disease, suicide, and sudden deaths [9, 10]. The WHO Global Palliative Care Atlas, the Lancet Commission on Pain and Palliative Care [11], and the World Health Resolution on Palliative Care [12] have all identified a critical gap between the need for, and provision of, palliative care (including bereavement care). However, within this gap, there is further inequity. Systematic reviews of the evidence in sub-Saharan Africa have found that bereavement interventions are rarely described within palliative care intervention studies [13, 14].

Community-based interventions using already existing structures, for example, local health cadres embedded in the local health system, are more effective and widely accepted within low-resourced countries such as Zimbabwe, whose socio-economic structures have vastly deteriorated [15]. Previous studies have shown that local health cadres trained to act as an extension of the central health centers are effective in health delivery as they increase coverage and access [16]. Caregivers from the communities that local health services serve can offer in-depth knowledge of local cultural preferences and practices for effective delivery and uptake of healthcare services [17–19].

This study will adopt the 9-cell bereavement intervention developed in Zimbabwe. The 9-cell was designed to assist individuals to reflect on their feelings in bereavement and identify resources in families and communities to manage bereavement. This process is intended to increase the lay supporter’s understanding of the experience of grief and to identify ways of increasing support to the bereaved. The 9-cell bereavement tool explores the communication that the bereaved currently receive, discussing and linking their own grief and bereavement experiences with the support they need at different stages [20]. This person-centered approach is designed to provide context-based, culturally appropriate, individually tailored support. The tool was implemented in Tanzania and India, with process data suggesting increases in awareness of the concepts behind grief and the bereavement process, providing rare opportunities to share experiences of both with fellow community members. One year after the 2004 Tsunami, an NGO funded a 10-week training and supervision program to integrate the 9-cell bereavement tool into the work of volunteer counselors in Tamil Nadu, India. Despite these examples of use, there has been no rigorous evaluation of the 9-cell [21].

There is an absence of effectiveness literature for bereavement interventions in sub-Saharan Africa [22–24]. However, the positive outcomes experienced in the few documented interventions, including the 9-cell bereavement tool as tested in other low-income countries similar to Zimbabwe, support the need for community-based bereavement interventions to be scaled up. With this knowledge and due to the potential vulnerability of bereaved individuals, the scarcity of resources within sub-Saharan Africa, it is essential to therefore establish the feasibility of delivering and testing the tool using a trial design, prior to investment and participant involvement in a full clinical trial.

## Methods

### Aim and objectives

The aims of this study are to assess the feasibility of implementing the 9-cell bereavement tool at the community level and to determine the feasibility of evaluating the intervention using a cluster randomized control trial design.

The objectives are (i) to determine the feasibility of conducting a randomized cluster trial in terms of recruitment and retention; (ii) to assess the feasibility of implementing the 9-cell bereavement tool; (iii) to determine whether there would be contamination between the clusters; (iv) to assess the acceptability and completeness of measures and data; (v) to identify trial participants’ views and experience of the intervention and its mechanisms of action; (vi) to estimate potential effect size; and (vii) to determine whether a full trial is warranted.

### Feasibility questions and success criteria

We will seek to answer the following research questions: (1) will we be able to recruit at least 75% of the suggested sample size of interventionists and trial participants interventionists within 3 weeks? In order to meet proposed trial timelines, we suggest trial recruitment criteria of recruiting community leaders within 1 week; interventionists within 1 week and the trial participants within 1 week; giving a total recruitment period of 3 weeks. (2) Will we be able to retain at least 75% of both the trial participants and the interventionists in the total duration of the study? (3) Can we deliver the 9-cell bereavement intervention as intended? (4) Will the processes of a randomized cluster trial be possible? (5) Does process data suggest that the anticipated effect is likely?

There is a paucity of guidance on setting progression criteria for feasibility and pilot trials [25]. Therefore, we draw on the MRC guidance that such criteria should be judged in light of all study findings and used to refine study design. Our recruitment and retention criterion of 75% was set in light of published feasibility trial criteria and reflects the nature of our population (i.e., they are community-dwelling bereaved individuals without any known serious health conditions and so we anticipate high retention).

## Study design

A cluster feasibility randomized control trial with nested qualitative focus groups will be used for this study. Cluster randomization would be required in a full trial as the intervention is delivered at the community level. Recruitment is estimated to take place over an estimated 3-week period. It will include approaching and sensitization of community leaders; identification and recruitment of interventionists; qualitative data collection (FGD 1) with recruited interventionists; and identification and recruitment of trial participants.

The data collection timeline as illustrated in Fig. 1 will be as follows:

**Table Taba:** 

Week 0	Baseline data collection from trial participants
	Randomization
	Administering intervention to the intervention group
Week 14	Midline data collection from trial participants
	Qualitative data collection (FDG 2) with the intervention group
Week 27	Endline data collection from trial participants
	Qualitative data collection (FDG 3) with the intervention group
	Qualitative data collection (FGD 4) from trial participants
	Administering intervention to control group

**Fig. 1 Fig1:**
[figure not shown]
Study flow chart

Figure 1 presents the study flow chart. This is followed by a narrative description of the data collection stages.

### Timeline

Interventions are more effective when administered closer (though not too soon) to the time of death of the loved one [26, 27]. Six to 18 months is a suitable period for administering bereavement interventions *inclusive* of their follow-up [26]. According to [name], the developer of the 9-cell bereavement tool, the 6-month mark usually represents a time when social support often fades and the reality of the loss sets in. Inclusion criteria (elaborated in the “Recruitment” section below) of *trial participants* will therefore be individuals in the community who have experienced the loss of a loved one in the past 6 months from the recruitment date (even where someone has been bereaved within a week of the study; by the time the study is finished it will be over 9 months, so they theoretically are still eligible as 6 to 18 months is a suitable period for administering interventions inclusive of their follow-up as indicated above).

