#### Stage 3: Recruitment of potential trial participants

The potential interventionists from each community will be tasked to identify 2 to 3 people according to the following criteria. Potential participants must be (a) at least 18 years old, (b) resident within their neighborhoods, (c) someone with whom they interact with on a daily basis, (d) whom they know to have been bereaved in the past 6 months, (e) would have the ability to either verbally consent or be able to consent in writing, (f) be able to read and write, and (g) be expected to attend and participate in the study. Potential participants who meet all of these criteria will be invited to a meeting where information regarding the study will be shared. Researchers will obtain consent from potential trial participants.

Following written informed consent, potential trial participants will be invited to participate in the study. Participating in the study includes completing questionnaires at baseline (T0, i.e., week 0), midline (T1, i.e., 3 months post-baseline or week 14), and endline (T2, i.e., 3 months post-midline or at week 27), with a subsample of the intervention cluster participants invited to qualitative focus group interviews to better understand participants’ views on study participation and intervention mechanisms of action. Focus group participants will be aged at least 18 years of age; be able to either verbally consent or be able to consent in writing; and be able to verbally share their experiences and thoughts regarding the study.

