## Data analysis

Quantitative data will be entered into a study-specific excel spreadsheet prior to import to SPSS for analysis.

In terms of recruitment, we will calculate the proportion of the target sample achieved for community lay interventionists and trial participants.

With respect to retention, we will calculate the proportion of potential trainees recruited who attended the full day training, and the proportion who remained active in bereavement support until trial end. We will report the proportion of trial participants who participate in T0 (baseline of week 0), T1 (midline at week 14 or 3 months post-baseline), and T2 (at week 27 or 3 months post-midline) data collection.

In terms of the outcome data, we will measure data completeness at each timepoint. We will plot data to check for floor and ceiling effects (to help us inform primary outcome selection), report data completeness, and plot means/standard deviations or medians and IQR (depending on data normality/symmetry of distribution) for each timepoint. We will appraise the selected outcome measures in terms of the qualitative explanation of perceived intervention benefits (and potential unintended consequences).

We will estimate potential treatment effect size using longitudinal methods for non-parametric data (no interim analysis), using an appropriate method (e.g., ANCOVA adjusting for baseline scores, with 95% confidence intervals). With regard to contamination, if we find that 8 km was a sufficient distance to minimize contamination, then we will (in full trial development) determine clusters that meet this criterion, which appears possible within Zimbabwe.

Verbatim transcripts of the individual and focus group interview data will be imported into NVIVO for analysis using the framework approach [44]. The trial participant and interventionist datasets will be analyzed separately. The thematic analysis will populate the framework by case analysis to generate themes, with the matrix permitting between-case comparison. Data will be integrated by appraising the quantitative outcomes in light of the qualitative description, with parity between the data types.

We will measure success in terms of our a priori criteria stated above, and if necessary refine methods by integrating the qualitative and quantitative data. If success criteria have not been met, refinements will aim to improve the design.

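### The only adjustment named for the effect size, baseline score, cannot allow for time since loss, although the plan expects support to fade at about 6 months and nearly all participants pass that point during follow-up

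*Protocol article*

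**What the plan says.** In the Timeline section the tool's developer is reported as saying that "the 6-month mark usually represents a time when social support often fades and the reality of the loss sets in". On that ground the section admits "individuals in the community who have experienced the loss of a loved one in the past 6 months from the recruitment date". Stage 3 of Recruitment applies the same window through the lay supporter, who names people "whom they know to have been bereaved in the past 6 months".

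Outcomes are taken at week 0, at "midline (T1, i.e., 3 months post-baseline or week 14" and at "endline (T2, i.e., 3 months post-midline or at week 27". They include a social support scale (MSSS) and a scale of current feelings about the loss (TRIG).

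Data analysis estimates the effect size "using an appropriate method (e.g., ANCOVA adjusting for baseline scores, with 95% confidence intervals". No other adjustment is named. The article does not mention time since loss again after the entry criteria.

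**The concern.** The plan's own account makes time since loss a driver of at least one outcome, social support, with a turning point at about 6 months. Entry at 0 to 6 months followed by about 6 months of follow-up puts that point inside the study for nearly everyone, but at a different study week for each person.

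The baseline score does not carry this information. Someone 1 month after the loss and someone 5 months after it can have the same T0 score, yet stand on opposite sides of the mark at T1. If one community's participants have older losses on average, more of them have passed the mark at T1, and ANCOVA on baseline score attributes the resulting difference to the intervention or to its absence.

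At stake is objective (vi), the potential effect size, which bears on objective (vii), whether a full trial is warranted.

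**Working it through.** **Inputs from the article.** Mark at 6 months; entry 0 to 6 months after the loss; visits at weeks 0, 14 and 27; two clusters, one per arm. The number per cluster is given as at least 75 in the Abstract and as 25 in Stage 4, so both are used. Recruitment timing: "interventionists within 1 week and the trial participants within 1 week; giving a total recruitment period of 3 weeks".

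**Assumptions, not in the article.** Loss dates evenly spread over the window, unless stated otherwise; a step change in support at 6 months of 0.5 SD, with 0.25 SD shown for range; no treatment effect.

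**The plan's own figure.** For someone bereaved within a week of the study, Timeline says "by the time the study is finished it will be over 9 months". With 365.25/12/7 = 4.348 weeks per month, (1 + 27)/4.348 = 6.4 months, or (1 + 3 + 27)/4.348 = 7.1 months with 3 weeks of recruitment added. The figure does not reproduce. That is a separate slip and nothing below depends on it.

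**When the mark is crossed.** 6 months = 26.09 weeks; T1 = 14/4.348 = 3.22 months; T2 = 27/4.348 = 6.21 months.

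- If recruitment and week 0 coincide, crossing falls between week 0 and week 26.1.
- Share past the mark at T1: 14/26.09 = 54%.
- At T2 everyone is past it, at 6.2 to 12.2 months since loss.
- With a gap between recruitment and week 0, some cross before baseline: 1/26.09 = 4% for 1 week, 3/26.09 = 11% for 3 weeks. The T1 share becomes 15/26.09 = 57% or 17/26.09 = 65%.

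**Size of the T1 distortion.** Nearly all baseline scores precede the mark, so under a step they are almost unrelated to time since loss. The spurious T1 difference is then about step × (difference between clusters in the share past the mark).

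The 95% chance range for that difference is 1.96 × √(2p(1−p)/n) with p = 0.537: 0.16 for n = 75 and 0.28 for n = 25.

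For assumed imbalances, a person is past the mark at T1 if the loss was more than 6 − 3.22 = 2.78 months before T0:

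- Losses at 0–5 versus 1–6 months: (5 − 2.78)/5 = 44% versus (6 − 2.78)/5 = 64%.
- Losses at 0–4 versus 2–6 months: (4 − 2.78)/4 = 31% versus (6 − 2.78)/4 = 81% (unrounded, 50 points apart).

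| Difference in share past the mark at T1 | Source | Step 0.25 SD | Step 0.5 SD |
|---|---|---|---|
| 16 points | chance, 75 per arm | 0.04 SD | 0.08 SD |
| 20 points | 0–5 vs 1–6 months | 0.05 SD | 0.10 SD |
| 28 points | chance, 25 per arm | 0.07 SD | 0.14 SD |
| 50 points | 0–4 vs 2–6 months | 0.125 SD | 0.25 SD |

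Simulated ANCOVA on baseline score, with the 0.5 SD step, gives 0.098 SD for the 20-point case and 0.246 SD for the 50-point case, in line with the table.

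**T2.** Under a step the spurious difference is about 0, since all have crossed. In a second simulation (75 per arm, correlation 0.5, 0.5 SD change, cluster means of time since loss 0.5, 1 or 2 months apart), a gradual change after 6 months gives 0.04, 0.08 and 0.16 SD at T2. A transient dip gives 0.05, 0.10 and 0.19 SD, in the opposite direction to T1.

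**Adding time since loss.** In the second simulation a linear term brings every figure to within 0.01 SD. In the first, linear and quadratic terms leave −0.032 SD (50-point case) and −0.046 SD (20-point case) under a step. If the same fall is spread over months 4 to 8, they leave 0.009 and −0.016 SD.

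**The case against.** The strongest reply is that the method sentence gives an example, that a full protocol or SAP may list more covariates, and that the participants' demographic form, whose items are not shown, may already ask for the date of death. A reader might infer that the plan excludes time since loss; the article does not say so. What stands is narrower: the one adjustment it names does not address the time effect that its Timeline section gives as the reason for the entry window.

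The premise is also soft. The article reports one expert's view of what usually happens, mentions no step and gives no size on any scale. It gives no direction or size for a change in TRIG. The 0.5 SD is an assumption, and so are the uneven loss windows. The communities are described as alike, the same recruitment procedure applies to both, and baseline precedes randomization, so supporters cannot select by arm. An imbalance of 50 points is therefore extreme. The chance-level distortions of 0.08 and 0.14 SD lie well inside the ANCOVA 95% half-widths, 1.96 × √(2(1−ρ²)/n): 0.23 to 0.28 SD at 75 per arm and 0.40 to 0.48 SD at 25, for ρ of 0.7 to 0.5 and ignoring clustering. All of this bears on size and stands.

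A reader might also infer that natural fading within each arm would pass for response. The wait-list arm exists to handle that, and the article plots the time-point summaries only descriptively.

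Finally, the numerical success criteria concern recruitment and retention, so the effect estimate does not by itself decide progression.

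**Conclusion.** The point holds as a mismatch between the plan's premise and its named adjustment. Nearly all participants pass the 6-month mark during follow-up, at a time that baseline score cannot capture. If the clusters differ in time since loss, the T1 effect estimate is distorted by about 0.08 to 0.14 SD at chance-level imbalances, and by 0.25 SD at an extreme one, under an assumed 0.5 SD step; a 0.25 SD step halves these.

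Two stronger readings go too far. One is that no one has passed the mark at T0 and every participant crosses it later: this fails for about 4% to 11% if recruitment precedes week 0 by 1 to 3 weeks. The other is that both follow-up estimates are biased: under a pure step only T1 is affected, and T2 needs a gradual or transient change, which the article does not describe. Nor does the article show that the clusters do differ in time since loss. The change is worth making because it is cheap and the estimate feeds the planning of a full trial.

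**What to change.** - Record the month of death from the participant at baseline, if the demographic form does not already. Eligibility needs this in substance, but at present rests on what the supporter knows.
- Put time since loss beside baseline score in the effect-size model, as a linear term with a quadratic or in bands, and state the form in advance.
- Report the distribution of time since loss by cluster.
- Optionally, show the T0, T1 and T2 plots by band, for example under 3 versus 3 to 6 months.

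The cost is one form item and one or two degrees of freedom. The text should also say what this does not do. It removes one measurable source of imbalance, not always completely if the functional form is wrong. With one cluster per arm it does not cure the confounding of arm with cluster.

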### Setting

This study will be conducted in Chitungwiza, a city bordering the capital city of Zimbabwe. A local supporting organization for this study, Island Hospice and Healthcare (IHH), has been involved in community work in Chitungwiza for the past 15 years engaging community groups, community leaders, non-governmental organizations (NGOs), churches, and government ministries.

Two broadly similar communities within Chitungwiza have been selected; one will act as the intervention group (IG) and the other as the control group (CG). Chitungwiza is densely populated with a large surface area, which greatly reduces potential contamination between the two selected intervention and control areas. Figure 2 provides the map of Chitungwiza; one community cluster is in the north-west section and the second is in the south-east, therefore reducing the likelihood of contamination. They have similar socio-demographic characteristics and value systems, with the economy being largely supported by informal trade and falling under the same traditional territory and health administration. The two communities selected within Chitungwiza are about 8 km apart. Through discussion with local stakeholders, 8 km is anticipated to be adequate distance and corresponding density to reduce possible contamination between the two clusters. However, as an added precaution, the control group will be asked at midline and at endline to establish whether they have visited the community where the intervention took place and if they had a discussion with any community member who received the intervention.

